### Knowledge, Self-Efficacy, and Burden

Linear mixed models will be used to assess the relationship between group assignment and score for each of the outcomes: the DKAS and its subdomains (causes and characteristics, communication and behavior, care considerations, and risks and health promotion), the RSCSE and its subdomains (obtaining respite, managing disruptive behaviors, and controlling upsetting thoughts), and the ZBI. All models will include the 2 stratification factors, education level (high school equivalent or less, some college or university, and college or university or graduate degree) and care partner type (care partner to a spouse, care partner to a parent, and care partner to someone other than a spouse or parent). Group assignment will be included as the primary independent variable of interest with interaction from time to determine how the relationship between outcome score and group assignment will change from baseline to follow-up. Potential effect modifiers, including age (categorized as <44 years, 45-64, and ≥65 years), gender, education level, stage of dementia (mild [early-stage] dementia, moderate [middle-stage] dementia, severe [late-stage] dementia, or “I don’t know”), and length of time as a care partner (less than 3 months, more than 3 months but less than 1 year, more than 1 year but less than 2 years, more than 2 years but less than 5 years, or more than 5 years), will be explored in relation to group assignment. These variables will be retained in the model if the likelihood ratio test indicates a significant difference between the nested model and the full model (*P*<.05). If they are not significant modifiers of the group-outcome relationship, then they will be investigated as effect modifiers with respect to time. An intention-to-treat analysis will also be performed and include all individuals as per group assignment. A per-protocol analysis will also be performed. Correlations between the number of lessons in the intervention completed and the DKAS score will be analyzed.

We will also look for inverse correlations between the DKAS and ZBI scores, as well as between the RSCSE and ZBI scores. Analyses will be performed using an α level of .05 and 2-sided tests. All analyses will be conducted using RStudio software (Posit).

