### Participants

#### Inclusion and Exclusion Criteria

Individuals who meet the following self-reported inclusion criteria will be invited to participate in the study: (1) family or friend care partner of a person living with dementia, (2) reside in Canada, (3) 16+ years of age, (4) able to read and listen to English, (5) access to email and internet, and (6) comfortable using email and internet. Participants who answer “yes” to all 6 questions using the research platform will be invited to read the study information and provide informed consent before creating a participant account.

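### The printed age bands (<44, 45-64, ≥65 years) leave eligible 44-year-olds in no band, so literal coding would drop them from any model that contains age

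*Protocol article*

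**What the plan says.** The eligibility list under Inclusion and Exclusion Criteria in the protocol article sets a lower age limit and no upper one: "3) 16+ years of age".

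Under Data Analysis, the section Knowledge, Self-Efficacy, and Burden lists the potential effect modifiers and gives the coding for age: "age (categorized as <44 years, 45-64, and ≥65 years". These variables "will be explored in relation to group assignment", and each is "retained in the model if the likelihood ratio test indicates a significant difference between the nested model and the full model", at P<.05. A variable that does not modify the group effect is then tested as a modifier of the time effect. The same section promises an intention-to-treat analysis that keeps everyone in the group to which they were assigned.

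The section Participant Characteristics also names age as a possible effect modifier, but without bands. The article does not say whether age was recorded in years or chosen from bands, or how an unclassified age would be handled.

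**The concern.** A categorical covariate needs bands that are exhaustive and do not overlap. The printed lowest band stops at 43 completed years and the next begins at 45. A participant aged 44 therefore meets the entry criteria but has no category.

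Coded literally, that person's age category is missing, and a standard mixed-model fit omits the person's records from any model with age in it. If age passes the retention test for an outcome, the model reported for that outcome excludes all 44-year-olds, for no reason connected with the trial. The rule applies to ten scores: the DKAS and its four subdomains (5), the RSCSE and its three subdomains (4), and the ZBI (1). A fit that leaves out randomised people because of a coding gap is not an analysis of all individuals as assigned.

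**Working it through.** **Inputs.** Age bands: <44, 45-64, ≥65 (Knowledge, Self-Efficacy, and Burden). Eligible ages: 16 and over (Inclusion and Exclusion Criteria). Randomised: 125 in run 1 (61 + 64) and 100 in run 2 (53 + 47), from Results. Share of participants aged 44: not given; assumed p = 1% to 3%.

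**Step 1: are the bands exhaustive?** Each age in completed years from 16 to 100 was assigned to the printed bands.
- 16 to 43: first band only.
- 44: not below 44 and not at least 45, so no band.
- 45 to 64: second band only.
- 65 to 100: third band only.

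Age 44 is the only unclassified age, and no age falls in two bands. With the lowest band read as ≤44 (equivalently <45 in completed years), every age falls in exactly one. This step needs no assumption.

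**Step 2: how many people?** Expected number = N × p.
- Run 1: 125 × 0.01 = 1.25 to 125 × 0.03 = 3.75.
- Run 2: 100 × 0.01 = 1 to 100 × 0.03 = 3.
- Both runs, if pooled: 225 × 0.01 = 2.25 to 225 × 0.03 = 6.75.

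**Step 3: is anyone likely to be affected?** Chance of at least one 44-year-old = 1 − (1 − p)^N.
- Run 1: 1 − 0.99^125 = 0.72 to 1 − 0.97^125 = 0.98.
- Run 2: 1 − 0.99^100 = 0.63 to 1 − 0.97^100 = 0.95.

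**Step 4: what does the software do?** A two-timepoint dataset of 100 participants, 4 of them aged 44, was simulated and fitted by maximum likelihood in R, with unbanded ages set to missing. The group-by-time model without age used 100 × 2 = 200 rows. Models containing age used (100 − 4) × 2 = 192 rows. The loss is thus confined to models with age in them. Two likelihood ratio comparisons were then tried.
- Age main-effect model against age-interaction model: both used the same 192 rows, so the test was valid.
- Model without age against age-interaction model: R's comparison function stopped with an error in both common mixed-model packages, because the fits used different numbers of observations.

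**The case against.** The strongest reply is that <44 is a typing slip. The other bands start at 45 and 65, so the intended lowest band is almost certainly ≤44 or <45. If the data were collected or coded that way, nobody is lost. This is plausible and makes the loss conditional, but nothing else in the article gives the bands and so confirms it. A probable slip in the only statement of a coding rule is still worth correcting.

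The second reply is that little depends on it. The modifier analysis is exploratory, effectiveness is a secondary outcome, and the conclusions say that the study was not powered to assess it fully. This stands and sets the severity.

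A reader might go further in two directions that the document does not support.

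- **That the likelihood ratio test is invalid because the two fits use different people.** A test of effect modification normally keeps the modifier's main effect in the nested model, and the article does not say otherwise. For a three-band modifier and a two-level factor, that test adds (3 − 1) × (2 − 1) = 2 parameters, and both fits exclude the same participants. The mismatch arises only if the nested model omits age altogether. The article names R through RStudio as its software, and there the standard comparison stops with an error and does not return a misleading P value.
- **That the caregiving-duration bands lose people in the same way.** The wording, "less than 3 months, more than 3 months but less than 1 year" and so on, leaves the exact boundary undefined. However, the categories read like questionnaire options, and the neighbouring dementia-stage list includes a don't-know response. If each respondent ticked one option, none is missing. The article does not confirm this, but neither does it show any loss.

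**Conclusion.** The point holds as a minor error in a stated analysis rule. The printed age bands do not cover age 44, although 44-year-olds are eligible. That much follows from the text alone.

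The consequence rests on two conditions: that age is held in years, and that the bands are coded as printed with unbanded ages left missing. Under those conditions, 44-year-olds leave every model that contains age, including the reported model for any outcome where age is retained, contrary to the intention-to-treat commitment. On the assumed share of 1% to 3%, that is about 1 to 4 people in run 1 and 1 to 3 in run 2. The base group-by-time models without age are untouched, and neither the validity of the likelihood ratio test nor the duration bands is called into question.

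**What to change.** Restate the lowest age band as 16-44 (<45) years, leaving 45-64 and ≥65 as they are, so that every eligible age falls in exactly one band. If age was collected in bands, print the options as participants saw them.

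The cost is a wording change and, where age is held in years, at most one line of recoding. No new data are needed. The article places the run 2 analysis in spring 2025, after data collection had ended. If the models have already been fitted, it is enough to check how 44-year-olds were coded and to refit the age models only if they were left out.

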### Participant Characteristics

Differences in participant demographics between groups will be assessed using unpaired 2-tailed *t* tests. Both stratification factors, care partner type (care partner to a spouse, care partner to a parent, and care partner to someone other than a spouse or parent) and level of education (high school equivalent or less, some college or university, and college or university or graduate degree), will be included in all models. In addition, age, sex, education, stage of dementia, and length of time as a care partner will be looked at as possible effect modifiers of the relationship between the group and the outcomes, and timepoint and the outcomes.

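### Effect modifiers are tested against group and then time instead of group-by-time, which dilutes the test of interest, and P<.05 retention lets models differ between scores by chance

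*Protocol article*

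**What the plan says.** The protocol article, under Knowledge, Self-Efficacy, and Burden, fits a linear mixed model to each score at baseline and 8 weeks. "Group assignment will be included as the primary independent variable of interest with interaction from time", so that the model shows how the arm difference moves between the two assessments. Both stratification factors are in every model.

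Five candidate modifiers are then handled in two steps. First, they "will be explored in relation to group assignment". They are "retained in the model if the likelihood ratio test indicates a significant difference between the nested model and the full model", with P<.05 as the limit. Second: "If they are not significant modifiers of the group-outcome relationship, then they will be investigated as effect modifiers with respect to time". Under Participant Characteristics the same candidates are described as "possible effect modifiers of the relationship between the group and the outcomes, and timepoint and the outcomes", that is, as two separate relationships.

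The general testing rule is: "Analyses will be performed using an α level of .05 and 2-sided tests". The article states no multiplicity adjustment for the modifier tests and no main model that stays the same whatever they show. The age bands are given as "age (categorized as <44 years, 45-64, and ≥65 years".

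**The concern.** With baseline and follow-up in one model, the intervention effect is group-by-time. A variable that modifies that effect shows itself in group × time × modifier. The plan, as worded, looks at two other terms.

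- Modifier-by-group is a difference averaged over T1 and T2. At T1 randomisation makes the expected arm difference zero in every subgroup, so half of the average carries no signal.
- Modifier-by-time is a difference in change averaged over the arms. A variable that goes with the same change in both arms gives the same kind of result as one that alters the intervention effect.

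Terms that pass P<.05 then stay in the model for that score, so the 10 reported models need not have the same form. The results are meant to help plan a larger trial. Modifiers that are missed, mislabelled or kept by chance could misdirect its stratification or target population.

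**Working it through.** The article gives no power or error rate for the modifier tests, so there is no figure to reproduce.

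**Inputs from the article**
- Assessments: 2 (Study Design).
- Candidate modifiers: age, sex (called gender in the later section), education, stage of dementia and time as a care partner = 5.
- Scores: DKAS total + 4 subdomains, RSCSE total + 3 subdomains, ZBI: 5 + 4 + 1 = 10.
- Test level: 0.05, two-sided.
- Expected completers: 80, 40 per group (Sample Size).

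**Assumptions, not in the article:** complete data, SD of 1 at both times, within-person correlation ρ from 0.3 to 0.8. For the power figures, also a balanced two-level modifier and a true modification δ of 1 SD at T2.

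**1. Dilution.** Modifier-by-group is estimated from each person's mean of T1 and T2: signal δ/2, SD √((1+ρ)/2). The three-way term is estimated from change: signal δ, SD √(2(1−ρ)). The design factor is the same, so

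z ratio = [(δ/2)/√((1+ρ)/2)] ÷ [δ/√(2(1−ρ))] = √((1−ρ)/(1+ρ)).

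| ρ | z ratio | sample multiple, 1/ratio² | power of modifier-by-group where the three-way test has 80% |
|---|---|---|---|
| 0.3 | 0.73 | 1.9 | 54% |
| 0.5 | 0.58 | 3.0 | 37% |
| 0.7 | 0.42 | 5.7 | 22% |
| 0.8 | 0.33 | 9.0 | 15% |

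The ratio does not depend on the sample size or on δ.

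**2. The two-step procedure.** Simulation with 80 completers and 5,000 runs per setting (percentages of all runs):

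| δ | ρ | modifier-by-group kept | then modifier-by-time kept | three-way term significant |
|---|---|---|---|---|
| 1 SD | 0.4 | 27% | 37% | 54% |
| 1 SD | 0.6 | 24% | 51% | 69% |
| 1 SD | 0.8 | 22% | 72% | 93% |
| 0 | 0.6 | 4.8% | 4.9% | 5.2% |

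Hand check at ρ = 0.6 with 20 per cell. Both SDs are √0.8, so both standard errors are √0.8 × √(4/20) = 0.40. Three-way: z = 1/0.40 = 2.5, power Φ(2.5 − 1.96) = 71%. Modifier-by-group: z = 0.5/0.40 = 1.25, power Φ(1.25 − 1.96) = 24%. Both agree with the simulation.

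In these settings a true modification of the intervention effect most often ends up filed as a modifier of time.

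**3. What modifier-by-time picks up.** Suppose there is no modification, but the variable goes with 0.5 SD more change in both arms. At ρ = 0.5 the SD of change is √(2 × 0.5) = 1. With 40 per modifier level the standard error is √(1/40 + 1/40) = 0.224, z = 0.5/0.224 = 2.24, and the term is significant with probability Φ(2.24 − 1.96) = 61%. That is correct detection of a time effect, but it says nothing about the intervention.

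**4. Chance retention.** First step: 5 × 10 = 50 tests, 50 × 0.05 = 2.5 expected. Second step: 50 × 0.95 × 0.05 = 2.375. Together about 4.9 across the 10 models. Per score, the chance of at least one chance term is 1 − 0.95⁵ = 22.6% after the first step and 1 − 0.95¹⁰ = 40.1% after both. The expected counts do not need independent tests. The probabilities do.

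**5. Effect on the main estimate.** In one simulated complete dataset (80 people, three-level modifier, random-intercept model), group-by-time was 0.264 (SE 0.187). Adding modifier-by-group left it at 0.264. Adding modifier-by-time moved it to 0.192, a shift of 0.072, or about 0.4 of its standard error.

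**The case against.** The best defence is that the article never writes out the full model of the likelihood ratio test. The group-outcome relationship could be read as the group-by-time relationship defined just before it, and exact terms are often left to an analysis plan. That reading cannot be excluded, but it is the less natural one: Participant Characteristics lists group and timepoint as separate relationships, and the fallback treats time as a separate step. Even on that reading, the retention rule and the fallback remain.

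Four stronger readings are tempting, and the documents do not support them.
- A reader might infer that modification of the intervention effect is not tested at all. Modifier-by-group keeps some sensitivity, 22% to 27% in the settings above.
- A reader might infer that variables passing the second step would be reported as altering the intervention effect. The article labels them as modifiers with respect to time.
- A reader might infer that the main treatment estimate is badly distorted. With complete data a kept modifier-by-group term leaves it essentially unchanged. A kept modifier-by-time term can move it, but one dataset does not show bias.
- A reader might infer that people aged 44 will be lost from the age models. The gap in the printed bands is real, but the survey coding is not shown, and it looks like a drafting slip.

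It is also fair that the magnitudes rest on an assumed ρ and a two-level modifier, and that the three-way test would itself be imprecise. With 80 completers spread evenly, five categories of caring time by two arms leave 80/10 = 8 per cell, and four stages leave 80/8 = 10.

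**Conclusion.** The concern holds for the procedure as worded: modification of the intervention effect is tested only through a diluted term, and the fallback addresses a different question. The dilution is a z ratio of 0.73, 0.58 and 0.42 at ρ = 0.3, 0.5 and 0.7. The formula is exact for complete two-time data with equal variances; the values of ρ are assumptions. The retention rule makes about 2.5 chance terms likely at the first step alone, so model form can differ between scores for no real reason.

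Severity is moderate. Effectiveness is a secondary objective, the modifier work is worded as exploration, and the article itself says that the study lacks the power to assess effectiveness fully. The primary feasibility outcome is unaffected. The age-44 gap is a minor drafting correction.

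**What to change.** - Fix one main model for every score: time, group-by-time (with the group term already planned) and the two stratification factors. No term enters or leaves it on the basis of a test.
- Assess each modifier in its own model, labelled exploratory, with group × time × modifier and all lower-order terms. Report the estimates with confidence intervals and carry nothing over into the main model.
- Delete the P<.05 retention rule and the fallback to time, and align Participant Characteristics with this.
- Say which age band takes 44-year-olds, for example by making the youngest band 44 years or younger.

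The cost is analysis wording and model code; no new data are needed. If the models have already been run as written, report the change as a deviation. The downside is that three-way terms will be imprecise in this pilot, above all for modifiers with four or five categories. The wide intervals should be shown as they are.

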## Methods

### Study Design

This study is a 2-arm, pilot, feasibility RCT with intervention and control groups. Participants will receive assessments at baseline (T1) and 8 weeks (T2).

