### Intervention and Control Groups

#### Baseline Assessments (Prestudy Surveys)

Both the intervention and control groups will receive access to the same prestudy surveys at T1 (baseline). The prestudy surveys will be used for the baseline assessments of participant demographics, knowledge, perceived self-efficacy, and perceived burden. Prestudy surveys will be identical for both the intervention and control groups.

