#### e-Learning Content

After completion of the prestudy surveys, the intervention group will receive access to 10 selected e-learning lessons from iGeriCare (Figure 1). The control group will receive access to a single e-learning lesson on “Promoting Brain Health.” Each group will be provided access to the other group’s e-learning content at the conclusion of the study. Specific lesson titles and outlines for the intervention and control groups are displayed in Table 1.

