### Feasibility of Implementation of the Intervention

We will examine intervention adherence as measured by lesson completion data and email open rates, level of technical and participant support required from the research team including tracking and sending reminders, participant satisfaction survey ratings, and exit interview data from a sample of participants from the intervention group.

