### Feasibility of the Study Methods

Study methods will also be evaluated. We will examine recruitment rate as measured by participants per day, participant acceptability of the intervention and surveys as measured by completion and attrition rates, time to complete the intervention and surveys, level of engagement and exposure to the intervention (including potential “fast trackers” moving through the intervention at a high speed), survey data, and exit interview data.

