**Figure 2 figure2:**
[figure not shown]
Study flow diagram for run 1.

Preliminary results showed a substantial number of participants who did not engage with the protocol as initially intended. A number of participants were identified as not having completed the protocol as intended, as demonstrated by “fast-tracking” through the e-learning (ie, clicking next without allowing time for reading or listening to content) or by repeatedly clicking “I don’t know” on prestudy or poststudy surveys.

Following this, a decision was made to recruit an additional cohort of participants (n=100) using learnings gained from the initial recruitment cohort concerns. A paid panel service, AskingCanadians, was engaged to assist with recruitment. AskingCanadians is a reputable paid panel service that was able to specifically target family and friend care partners of people living with dementia.

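### The planned correlation of lessons completed with the DKAS score does not use baseline DKAS, so if baseline knowledge is related to lesson completion it can show or hide a dose-response wrongly

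*Protocol article*

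**What the plan says.** The section on analysis of knowledge, self-efficacy and burden gives this analysis one sentence: "Correlations between the number of lessons in the intervention completed and the DKAS score will be analyzed". It names a count as the exposure, a score as the outcome and correlation as the method. It gives no time point, change score or covariate. The same section sets the test level: "Analyses will be performed using an α level of .05 and 2-sided tests".

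Elsewhere the article establishes the following.

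- Study Design: "Participants will receive assessments at baseline (T1) and 8 weeks (T2").
- Baseline Assessments: "The prestudy surveys will be used for the baseline assessments of participant demographics, knowledge, perceived self-efficacy, and perceived burden". T1 DKAS is therefore available in both groups.
- e-Learning Content: "the intervention group will receive access to 10 selected e-learning lessons from iGeriCare", so the count runs from 0 to 10.
- Feasibility of Implementation: "intervention adherence as measured by lesson completion data and email open rates". No minimum time or engagement is attached to completion.
- Feasibility of the Study Methods lists "time to complete the intervention and surveys, level of engagement and exposure to the intervention" as items to examine, and mentions fast trackers there. It does not link them to the correlation.
- Results, initial cohort: some run 1 participants were found "clicking next without allowing time for reading or listening to content", and others answered repeatedly that they did not know.

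The two stratification factors, care partner type and education, are to enter all models. In context this concerns the linear mixed models. Those models also use baseline scores, through the group-by-time interaction. The correlation does neither as written.

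**The concern.** Group assignment is randomised, but the number of lessons completed within the intervention arm is not. Prior knowledge or education may influence both how many lessons a carer finishes and how the carer scores at 8 weeks. A correlation that leaves out T1 DKAS mixes that selection with any effect of the lessons. The mixing can go either way: keen, well-informed carers could produce a dose-response that is not there, and carers who study more because they know less could conceal one that is.

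The article says that the pilot will help plan a larger trial. A spurious or masked association between lessons and knowledge could influence how many lessons that trial delivers. The adjustment needs no new data, because the T1 score is already collected.

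**Working it through.** The plan states no figure for this correlation, so there is none to reproduce.

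**Inputs from the article.** Two-sided α of .05; 10 lessons; an expected 40 analysable participants per group (Sample Size). The intervention arms randomised were 61 (run 1) and 53 (run 2), which are upper limits because they allow for no loss.

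**Assumptions not in the article.** Correlation a between baseline DKAS and lesson count: 0.2 to 0.4, or the same sizes with negative sign. T1–T2 DKAS correlation ρ: 0.5 to 0.7.

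**1. No lesson effect, better-informed carers do more lessons.** If lessons do nothing, the only path from lesson count to T2 score runs through baseline, so the expected raw correlation is r = a × ρ.

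- Central case: 0.3 × 0.7 = 0.21.
- Range: 0.2 × 0.5 = 0.10 to 0.4 × 0.7 = 0.28.

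The chance of P<.05 by Fisher's z is about Φ(√(n−3)·atanh(r) − 1.96), plus a small opposite tail.

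- n=40, r=0.21: √37 × 0.213 = 1.30; Φ(1.30 − 1.96) = Φ(−0.66), about 25%.
- n=40, r=0.10: √37 × 0.100 = 0.61; Φ(−1.35) plus the opposite tail, about 9%.
- n=40, r=0.28: √37 × 0.288 = 1.75; Φ(−0.21), about 42%.
- n=61, r=0.21: √58 × 0.213 = 1.62; Φ(−0.34), about 37%. This assumes no dropout in run 1.

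A simulation with 3,000 trials per setting and a lesson count limited to 0–10 agrees. At n=40, significant results in the positive direction alone (nominal 2.5%):

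| a | ρ=0.5 | ρ=0.7 |
|---|---|---|
| 0.2 | 9% | 12% |
| 0.3 | 16% | 25% |
| 0.4 | 23% | 42% |

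After adjustment for T1, the two-sided rejection rate is 4% to 6% in every cell.

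**2. Real effect, less-informed carers do more lessons.** Take a = −0.3, ρ = 0.7 and a true effect of 0.3 SD per 3 lessons (3 lessons being 1 SD of the count before rounding and capping). On standardised scales, the covariance of lessons with T2 is 0.7 × (−0.3) + 0.3 = 0.09, and the variance of T2 is 1 + 0.09 − 2 × 0.7 × 0.3 × 0.3 = 0.964. So r = 0.09/√0.964 ≈ 0.09. With the count rounded and capped at 0–10, the simulated mean is 0.06. Power at n=40 is 6% raw against 57% adjusted for T1.

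**3. Baseline unrelated to lesson count (a = 0).** The raw correlation keeps its error rate of about 5%. With the same true effect, power at n=40 is 38% raw against 62% adjusted. The cost is power, not bias.

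**4. Clicked-through lessons.** This step is conditional, because the article does not define a completed lesson. Suppose fast trackers are logged as finishing all 10 lessons and learn nothing, the true effect is 0.4 SD per 3 lessons, a = 0, ρ = 0.7 and n=40. The mean raw correlation falls from 0.33 with no fast trackers to 0.08 with 20%. Adjustment for T1 alone gives a partial correlation of 0.10 at 20%. Adjustment plus exclusion of the fast trackers gives about 0.45. The 20% is illustrative.

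**The case against.** The strongest reply is that this is one sentence on an ancillary analysis in a condensed article. Time point, covariates and population may sit in a fuller plan that is not shown, and the score could mean T2 or change. Part of this stands: how a completed lesson is defined is such a detail, and its absence is no error in itself. But the sentence does state a method, and that method has no baseline term. Reading the score as change would not cure the problem. With equal SDs and no lesson effect, the correlation of lesson count with change is −a√((1−ρ)/2) = −0.3 × √0.15 ≈ −0.12, so the bias changes sign and does not vanish.

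A second reply is that the sizes rest on assumed correlations, that even the sign of a is unknown, and that 61 ignores dropout. This stands in full. The inflation exists only if baseline knowledge is related to lesson count.

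Three stronger readings are tempting but unsupported.

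- A reader might infer that fast-tracked lessons count as completed. The article says neither that they do nor that they do not. A per-protocol analysis is planned and may deal with them, although it is not tied to this correlation.
- A reader might infer that fast-tracking was frequent. The Results describe a substantial number of non-engaged participants but pool fast-tracking with repeated don't-know answers, and the Limitations pool fast trackers with fraudulent entrants. No proportion is given, and run 2 was recruited through a panel to reduce the problem.
- A reader might infer that the trial's effectiveness result is compromised. The comparison between randomised groups does not use lesson counts and is unaffected.

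**Conclusion.** The point holds in a limited form. As written, the analysis correlates a self-selected exposure with the DKAS score and leaves out a baseline measure that the trial has. With assumed correlations of 0.2–0.4 (baseline with lessons) and 0.5–0.7 (T1 with T2), a null lesson effect would give P<.05 in about 9% to 42% of trials at n=40, and about 25% in the central case, instead of 5%. With selection in the opposite direction, a real effect can be largely hidden. With no selection, the loss is power only. The consequence is confined to any dose-response statement drawn from a feasibility pilot that the article itself describes as not powered to assess effectiveness fully. The handling of clicked-through lessons is an open question in the document, not a demonstrated fault.

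**What to change.** Replace the correlation sentence with a regression, within the intervention arm, of T2 DKAS on number of lessons completed, adjusted for T1 DKAS, care partner type and education level. State that the result is an exploratory, non-randomised association.

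As an optional sensitivity analysis, where the time data allow, repeat the regression without participants identified as fast trackers, and say whether a clicked-through lesson counts as completed. The article plans to examine time to complete the intervention, but it does not say that time is logged per lesson, so a rule per lesson may not be possible. Fast trackers in run 1 had already been identified when the article was written, so a cut-off for that run cannot be presented as chosen before the data were seen. Excluding them also does not remove self-selection.

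The cost is wording, with no new data. The model has 7 coefficients (intercept, lessons, T1 DKAS and two for each three-level factor), which leaves 40 − 7 = 33 residual degrees of freedom at the planned 40. The article's Future Results section puts the analysis of run 2 still ahead.
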